#### Participation and reach

Participation will be assessed by collating the actual number of participants recruited versus the number invited to participate. Reach will be assessed by investigating the representativeness of study participants in regards to gender, age, ethnicity, socio-economic position (SEP) (compared to aggregate demographics of workforce in participating departments).

#### Responsiveness

We will assess the experiences of participation, aspects of acceptability for those who engaged versus those who didn’t, and any barriers or facilitators to this. This will draw on exit questionnaires completed at 6 months to assess level of engagement and focus groups at 6 months (n = 5) which will explore their experiences of the intervention and determine the types of participants who benefitted from the intervention, how and why it worked for them. We will purposively sample participants (maximum n = 10/group) to ensure a representative sample, including those actively engaged in the intervention and those not (i.e. dropped out) are recruited. Focus groups will be repeated at 18 months to ascertain the views of those who have maintained behaviour change and those who have not, and why. A schedule of open-ended questions will be used to elicit information about reactions to the intervention; barriers to physical activity and; suggestions for future roll-out of the intervention if proven effective. The final focus group will seek confirmation of the results from the previous focus groups via triangulation of the data. Semi-structured interviews with senior managers of participating employers (n = 7) and participating retailers (n = 5) will be used to explore their perceptions of being involved in the study.

#### RE-AIM framework

All data will be interpreted in the context of the RE-AIM framework [81].

This will ensure that we have a clearer understanding of the **R**each, **E**ffectiveness, **A**doption, **I**mplementation and **M**aintenance. This framework allows concurrent evaluation of dimensions considered relevant to ‘real world’ implementation, such as the capacity to reach target population and to change physical activity. In particular, we will examine differences across social groups and whether the intervention has impacted on inequalities in physical activity participation in the study population.

### Statistical analysis

For the primary analysis, mean steps per day at 6 months will be the dependent variable. A random intercept will be fitted at the cluster level (all other variables will be fixed effects), with group, organisation (in categories), and baseline mean steps per day added to the model (Objective 1). The main focus for the analysis will be the estimated coefficient representing the difference in mean steps per day between the Intervention and Control Group, adjusted for baseline differences. The model will then be extended through the inclusion of interactions involving group and relevant covariates to test for any differential effects of the intervention (e.g. age, sex, SEP, time discounting function). In light of the multiple testing involved, these subgroup analyses will be cautiously reported as hypothesis generating rather than confirmatory.

The primary analysis will then be repeated using 18-month follow-up data to investigate the effectiveness of the intervention for behaviour change maintenance (Objective 2). These analyses will be repeated with secondary health and wellbeing outcomes, and work-related outcomes (Objective 4 and 5). Further, sensitivity analyses will assess the impact of missing data using Multiple Imputation by Chained Equations (MICE), testing first whether missingness-at-random is plausible [82].

#### Mediation analyses

Mediation analyses of early behaviour change (uptake and initiation) (4 weeks) and behaviour change maintenance (6 months from start of intervention and 12 months from cessation of intervention) will be conducted (Objective 6). Methods for assessing and estimating the direct/indirect effects of intervention in the presence of multiple mediator models will be employed [83]. Bootstrap re-sampling strategies will be used to avoid multivariate normality assumptions in placing confidence limits on the estimates of the proportion of the total intervention effect that is mediated [84]. However, these analyses must be interpreted cautiously given the limitation that the mediation model is assumed to be correctly specified both in functional form and in that no variables are omitted which affect the relationships between independent and mediator or between mediator and dependent variables.

Briefly, social networks will be constructed from the work colleague nomination data at baseline, 6 and 18 months using UCINet 6.9 [85]. These data will be supplemented by objective, real-time proximity data collected throughout the 6 month intervention period. Individual-level network variables, for example, density and centrality measures, will be derived and included in mediation analyses. Further analyses investigating the structure, characteristics, function and evolution of workplace social networks on physical activity behaviour change will be undertaken as part of a NIHR Career Development Fellowship.

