The UK and US Governments [13, 14] have encouraged the use of incentives for promoting healthy lifestyles. The use of financial incentives for health-related behaviour change has been met with some scepticism [15], although their acceptability may be contingent on various factors, such as their effectiveness, type, and the target behaviour [16]. There is evidence to support the use of financial incentives for the initiation of behaviour change, for example, smoking, substance abuse [17–20]. Further, recent research has demonstrated evidence of financial incentives for single, one-off heath behaviours, such as vaccinations [19], and encouragingly, habitual health-related behaviour change [20]. However, the evidence for their effect on other health behaviours is sparse. Some financial [21] and non-financial incentives [22] have been shown to increase levels of physical activity, at least in the short-term and mainly with respect to structured exercise programmes [22], rather than free-living physical activity. There is a wealth of evidence on reinforcement of behaviour that shows that whilst incentives may be effective at changing behaviour, the effects are unlikely to be maintained when the incentives are withdrawn in the absence of other interventions [23]. Therefore, financial incentives alone may not be sufficient to promote maintained physical activity behaviour change, but may do so when embedded within an evidence-based, theoretically-driven intervention [16]. Further, financial incentive interventions designed using behavioural economic concepts have been shown to be effective for changing behaviour [24]. There is also limited evidence around the cost-effectiveness of interventions to promote physical activity in the workplace [25, 26], or indeed the cost-effectiveness of financial incentive-based interventions [19]. Therefore, to address such gaps in the evidence base and following the successful completion of a pilot study [27], we aim to conduct a cluster RCT of a complex intervention incorporating financial incentives to encourage physical activity and maintained behaviour change.

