### Update on study progress

During the recruitment phase for the study, a revised power calculation was undertaken assuming a less demanding effect size estimate taken from the recent literature together with our actual baseline data on mean and variance of cluster size and an intra-class correlation co-efficient of 0.029. In the original protocol, the sample size calculation for the trial was determined using an anticipated effect size of d = 0.21 (based upon a previous meta-analysis of workplace based physical activity interventions). However none of the included studies were incentive-based interventions for physical activity. More recent literature has been published [99, 100], including a meta-analysis in which a mean effect size for incentive based interventions of 16 min of MVPA per day was estimated, equating to an effect size of approximately 1600 steps (d = 0.40). Additionally, in the TRIPPA study [100], which is examining the influence of financial incentives on the effectiveness of a wireless-upload pedometer to encourage weekly physical activity goals, the study was powered to detect a difference of a minimum of 30 min of MVPA per week between groups and power calculations were based on considerably higher effect size than assumed in our original protocol (0.35). Therefore, under the assumption that our original estimate was too conservative, the power calculation has been updated. For an effect size of 0.40, a study of 330 per group (or 660 in total) would have 90 % power at the 5 % significance level. Assuming a 15 % drop-out, the study would need to randomise 776 participants.

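### The bootstrap confidence limits in the mediation analysis are placed on the proportion mediated, a ratio that becomes unstable whenever the total effect is not clearly different from zero

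*Protocol article*

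**What the plan says.** The protocol article (Mediation analyses, serving Objective 6) plans to estimate direct and indirect effects: "Methods for assessing and estimating the direct/indirect effects of intervention in the presence of multiple mediator models will be employed". It then names an interval method: "Bootstrap re-sampling strategies will be used to avoid multivariate normality assumptions". The use to which that method is put is given as "placing confidence limits on the estimates of the proportion of the total intervention effect that is mediated". The proportion mediated is the only quantity for which confidence limits are named.

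The analysis is applied at 4 weeks for uptake and initiation, and then for "behaviour change maintenance (6 months from start of intervention and 12 months from cessation of intervention"). The last of these is the 18-month visit.

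The section asks for cautious interpretation, but for a different reason: "given the limitation that the mediation model is assumed to be correctly specified both in functional form" and that no relevant variable is left out. It says nothing about a total effect that is small or close to zero.

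**The concern.** The proportion mediated divides the indirect effect by the total effect. A ratio is well behaved only while its denominator stays well away from zero. Resampling removes the normality assumption, which is the reason the article gives for using it, but it does nothing about a denominator whose sampling distribution straddles zero. Some resamples then have a total effect near zero or of the wrong sign, and the ratio jumps to large positive or negative values.

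A percentile interval still prints two finite numbers, so the problem is easy to miss. Objective 6 asks what mediates initiation and maintenance. A mediator with a usefully precise indirect effect could look uninformative, or carry a proportion that makes no sense, only because of the scale chosen for the summary.

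**Working it through.** **Inputs.** From Update on study progress: d = 0.40, about 1600 steps; 330 per group; 90% power; 5% significance; intra-class correlation 0.029; 15% drop-out; 776 randomised; an earlier design value of d = 0.21, and 0.35 as the value used in another incentive trial. A two-sided test is assumed.

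**The plan's own figure.** Without clustering, n per group = 2 × (3.242/0.40)² = 131.3, so 132, where 3.242 = 1.960 + 1.282. The ratio 330/132 is a design effect of 2.50. At the stated intra-class correlation, equal clusters would need 1 + 1.50/0.029 ≈ 53 people each. The article does not print the mean and variance of cluster size, so 330 can be neither confirmed nor refuted. The drop-out step reproduces: 660/0.85 = 776.5.

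**Standard error of the total effect.** Taking the stated power as correct, SE = 0.40/3.242 = 0.1234 SD. The implied SD is 1600/0.40 = 4000 steps, so the SE is about 494 steps/day. Equal precision at 18 months is assumed.

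**Probability that the total effect is not significant.** With λ = d/SE, P = Φ(1.96 − λ) − Φ(−1.96 − λ). This is also the probability that the 95% Fieller set for a ratio with this denominator is unbounded, because that set is bounded only if the denominator differs from zero at 5%.

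| True total effect d | λ | P(not significant) |
|---|---|---|
| 0.40 | 3.24 | 10% |
| 0.35 | 2.84 | 19% |
| 0.30 | 2.43 | 32% |
| 0.21 | 1.70 | 60% |
| 0.10 | 0.81 | 87% |
| 0 | 0 | 95% |

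The 50% point is d = 1.96 × 0.1234 = 0.242, or about 970 steps/day.

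*Sensitivity.* If baseline adjustment improves precision beyond the power calculation, with an assumed correlation of 0.6, the SE is 0.1234 × √(1 − 0.36) = 0.0987. The probability is then 43% at d = 0.21. At d = 0.40, λ = 4.05 and it is about 2%. More drop-out by 18 months would push the other way.

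**What the bootstrap would print.** An illustrative simulation used one mediator, a true proportion of 0.40, independent observations at 132 effective per arm, 300 data sets and 1000 resamples with percentile limits. Widths for the proportion are on its own scale; widths for the indirect effect are in SD.

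| d | Total effect | Median width, proportion | Limits outside 0 to 1 | Median width, indirect effect |
|---|---|---|---|---|
| 0.40 | significant | 0.65 | 40% | 0.21 |
| 0.40 | not significant | 5.4 | 100% | 0.20 |
| 0.21 | significant | 0.94 | 64% | 0.14 |
| 0.21 | not significant | 8.9 | 100% | 0.14 |
| 0.10 | significant | 0.89 | 85% | 0.13 |
| 0.10 | not significant | 5.8 | 100% | 0.11 |

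The interval for the indirect effect hardly changes with the significance of the total effect, while the interval for the proportion widens roughly six- to nine-fold. The simulation is small (about 30 data sets lie behind the non-significant row at d = 0.40) and shows widths only. The statement on coverage rests on the Fieller result: where the valid set is unbounded, an interval that is always finite cannot be relied on to cover at its nominal level.

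**The case against.** **Direct and indirect effects are already planned.** They are, and nothing excludes intervals for them. The proportion is therefore not the only summary, and a well-estimated indirect effect need not be lost. This stands and limits the harm. It does not remove the point, because the article commits its named confidence limits to the proportion.

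**This is detail for the analysis plan.** The bootstrap type, the resampling unit and reporting rules often belong there, and their absence is not criticised. The quantity that receives the limits is stated in the article, so it can be assessed.

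**A reader might infer that a null total effect is the likely case at 18 months.** The documents do not support this. The Background remark that "the effects are unlikely to be maintained when the incentives are withdrawn" is immediately limited to incentives without other interventions, and the text goes on to say that incentives embedded in a theory-driven programme, as here, may sustain change. The trial is powered on "equating to an effect size of approximately 1600 steps (d = 0.40"). The original calculation was "determined using an anticipated effect size of d = 0.21", and the article sets that value aside as too conservative. The Background does report scant long-term benefit from earlier workplace interventions, which makes a smaller effect plausible but puts no number on it.

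**A reader might also infer that no bounded interval will be obtained.** That describes the Fieller set. The planned bootstrap will print finite limits, and their great width would itself signal imprecision to an alert reader. What remains is that such limits are hard to interpret and their nominal coverage cannot be trusted.

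**The analysis is secondary and already flagged for caution.** Both are true, although the caution concerns model specification and not a small denominator.

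**Conclusion.** The point holds in a limited form. The article places its bootstrap limits on a ratio that degrades whenever the total effect is not clearly different from zero, and it has no safeguard for that case. On the trial's own power statement, the chance of this at a given time point runs from about 10% if d = 0.40 is achieved and maintained, through 60% at d = 0.21, to 95% if there is no effect. The 50% mark lies near d = 0.24.

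These figures assume that the stated 90% power is right, that testing is two-sided and that precision at 18 months equals that at 6 months. They do not show that a non-significant 18-month effect is probable, since the article gives no 18-month effect size. The consequence is confined to how Objective 6 is reported; the 6-month primary result and the 18-month effectiveness comparison are untouched.

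**What to change.** Change the sentence on confidence limits so that the bootstrap intervals, resampling whole clusters to respect the randomisation, are placed on the indirect and direct effects on the outcome scale (steps/day where steps are the outcome). Make these the main mediation result.

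Keep the proportion mediated as a secondary descriptive figure. Always show it beside the total effect and its interval, and state that it is not interpretable when that interval includes zero. This is preferable to printing the proportion only when the total effect is significant: that rule would select data sets with overestimated denominators and tend to bias the quoted proportions downward.

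The cost is one sentence of text and no new data. The loss is that the proportion, which is easy to communicate, is no longer the headline summary.

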**Methods/design:**

This cluster randomised control trial will recruit 776 office-based employees from public sector organisations in Belfast and Lisburn city centres, Northern Ireland. Participants will be randomly allocated by cluster to either the Intervention Group or Control Group (waiting list control). The 6-month intervention consists of rewards (retail vouchers, based on similar principles to high street loyalty cards), feedback and other evidence-based behaviour change techniques. Sensors situated in the vicinity of participating workplaces will promote and monitor minutes of physical activity undertaken by participants. Both groups will complete all outcome measures. The primary outcome is steps per day recorded using a pedometer (Yamax Digiwalker CW-701) for 7 consecutive days at baseline, 6, 12 and 18 months. Secondary outcomes include health, mental wellbeing, quality of life, work absenteeism and presenteeism, and use of healthcare resources. Process measures will assess intervention “dose”, website usage, and intervention fidelity. An economic evaluation will be conducted from the National Health Service, employer and retailer perspective using both a cost-utility and cost-effectiveness framework. The inclusion of a discrete choice experiment will further generate values for a cost-benefit analysis. Participant focus groups will explore who the intervention worked for and why, and interviews with retailers will elucidate their views on the sustainability of a public health focused loyalty card scheme.

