### Intervention

#### Intervention group

The Physical Activity Loyalty (PAL) scheme is a complex multi-component intervention based on concepts similar to those that underpin a high-street loyalty card aimed at encouraging repeated behaviour (i.e. loyalty) [24] and is designed to incorporate a range of behaviour change techniques. Components include the provision of ‘points’ and rewards (financial incentives) contingent on meeting targeted physical activity behaviour goals (extrinsic motivation, goal-setting). Participants will be encouraged to undertake 150 mins/week of physical activity which is in line with current guidelines [33]. The PAL scheme integrates a novel physical activity tracking system with web-based monitoring and evidence-based behaviour change tools (i.e. self-monitoring, goal-setting). The proposed 6-month intervention will involve placing sensors (wifi beacons) in the vicinity of participating workplaces at specific locations to encourage physical activity within a 2 km radius of participants’ worksites (see Fig. 1) (i.e. provision of prompts/cues, habit formation, addition of objects to the environment). Locations include along footpaths, local parks, leisure centre, shopping mall, bus stops and train stations. Maps of various walking routes and details about physical activity opportunities tailored to the workplace will be provided on the study website (instruction on how to perform behaviour) [34]. Participant’s activity will be logged when they pass within an approximate 25 m radius of the wifi sensors with their PAL keyfob when undertaking physical activity (e.g. walking). This logs the place, date and time of the bout of activity. Participants can log onto their account on the study website and receive real-time feedback on minutes of their physical activity. Minutes will be converted to ‘points’ (10 ‘points’ for 1 min of activity recorded), and collected ‘points’ are redeemable for rewards (downloadable retail vouchers) sponsored by, and redeemable at, local businesses. To reduce the risk of ‘gaming’, a daily ‘points’ cap will be implemented and the transit times between sensors checked for anomalous values [27]. Bonus rewards and ‘Double Points Days’ will be offered when participants meet specific weekly physical activity targets. [17].

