#### Mediators/moderators

We will collect data that are hypothesised to mediate loyalty scheme use, initiation (4 weeks) and maintenance of physical activity behaviour (6 months post-baseline). It is hypothesised that change in mediators should be apparent at 4–6 weeks and that mediators of early behaviour change are distinct from those affecting maintenance [52–54]. These theoretical constructs and associated outcome measures have been informed from the mapping of BCT’s from the pilot study and evidence from the relevant literature on behavioural initiation and maintenance [55–60]. Common core theoretical constructs of behaviour change including outcome expectancy [61], self-efficacy [62] and intention [63], motivation, financial motivation, planning, subjective norms, stated WTP and WTA derived from the DCEs, will be collected at baseline and 4 weeks to assess incentives to initiate behaviour change. Subjective social network data will be collected by work colleague nominations, with participants asked to nominate up to five colleagues that they usually socialise with and would also partake in physical activity with at baseline and, 6 and 18-months follow-up. Furthermore, social networks will be inferred when user’s keyfobs are “sensed” at sensors placed at physical activity opportunities in the vicinity of participating workplaces [64]. Perceptions of workplace environment [65] and objective measures of the workplace environment using Geographical Information Systems (GIS) data including walkability [66], street connectivity, access to physical activity opportunities (shops, parks, leisure facilities, train/bus stations) will be measured [67] at baseline. Other measures of web engagement, confidence in using the internet and loyalty scheme usage which may mediate intervention “dose” [68] and therefore behaviour change have been included.

To assess mediators of behaviour change maintenance, habit using the Self-Report Habit Index [69], recovery and maintenance self-efficacy [70], social norms [71], satisfaction with outcome expectancies [61], motivation, planning and social support, stated WTP and WTA, will be captured at baseline and 6 months. Data on inter-temporal and risk preferences will be collected at 6 months only (immediate post-intervention). In addition, subjective social network data will be collected at 6 and 18 months.

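### Keyfob proximity ties appear to exist only in the intervention arm during months 0–6, so network variables that use them are not comparable between arms in the mediation models

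*Protocol article*

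**What the plan says.** Two sources of network data are planned.

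- **Nominations.** The Mediators/moderators section describes self-report, "with participants asked to nominate up to five colleagues that they usually socialise with and would also partake in physical activity with", at baseline, 6 and 18 months. That section sits under Outcome measures, and the abstract says "Both groups will complete all outcome measures", so nothing limits nominations to one arm.
- **Proximity.** The same section adds that "social networks will be inferred when user’s keyfobs are “sensed” at sensors placed at physical activity opportunities in the vicinity of participating workplaces". The keyfob itself is introduced under Intervention group: "Participant’s activity will be logged when they pass within an approximate 25 m radius of the wifi sensors with their PAL keyfob".

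Under Mediation analyses, "social networks will be constructed from the work colleague nomination data at baseline, 6 and 18 months using UCINet 6.9". The next sentence reads "These data will be supplemented by objective, real-time proximity data collected throughout the 6 month intervention period", and the one after it "Individual-level network variables, for example, density and centrality measures, will be derived and included in mediation analyses". The same section says these analyses estimate direct and indirect effects of the intervention and the share of its total effect that is mediated, for initiation (4 weeks) and for maintenance (6 months, and 12 months after the intervention stops).

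Under Control group, the waiting-list arm completes the outcome measures and is offered the scheme only after the 18-month follow-up.

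**The concern.** A mediation analysis of a randomised contrast multiplies two paths: group to mediator, and mediator to outcome given group. The first path is interpretable only if the mediator is measured in the same way in both groups. Here one of the two network sources is a by-product of the intervention's own tracking system, which the section on fidelity and dose also uses to record exposure and compliance. A network variable that draws on it would be larger, or simply different, in the intervention arm even if no working relationship had changed.

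The second path is also at risk. A keyfob is logged only when its carrier passes a sensor, so people who walk more have more chances to acquire ties, and walking is what the primary outcome measures. Together, the two paths could lead the trial to report that social networks carried part of the effect when the result came from the measurement.

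**Working it through.** The document gives no figure on this point, so there is none to reproduce. The check has two parts: setting the sections side by side, and an illustration of what follows.

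**1. Who can generate which ties, and when**

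| Source | Intervention arm | Control arm | Timing |
|---|---|---|---|
| Nominations | yes | yes | baseline, 6, 18 months |
| Keyfob proximity | yes | none described; scheme offered after month 18 | months 0–6 |

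No section gives controls a keyfob, confines proximity data to a within-arm analysis, or keeps the two kinds of variable apart.

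**2. The group-to-mediator path**

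Let N be nominations, P proximity ties, G the arm and M = N + P. P is 0 in controls. If the intervention changes no relationship, N has the same mean in both arms, and

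a = E(M | G=1) − E(M | G=0) = E(P | G=1) = λ.

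The arm difference is the mean number of proximity ties, whatever that is. If P is kept as a separate variable, it is zero or missing for every control, and the same problem remains.

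**3. The mediator-to-outcome path**

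With equal arms, b is the pooled within-arm covariance of M and Y divided by the pooled within-arm variance of M. Controls contribute no covariance when there is no true network effect, so b depends entirely on whether P tracks activity in the intervention arm.

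Assumptions not in the document: N ~ Binomial(5, 0.5), with variance 1.25; P ~ Poisson with mean λ = 3 and log rate rising by ρ per SD of the participant's own activity; Y in SD units. Then

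- covariance in the intervention arm = 3ρ, pooled = 1.5ρ
- variance of P = 3 + 9(exp(ρ²) − 1)
- b = 1.5ρ / {1.25 + ½[3 + 9(exp(ρ²) − 1)]}
- indirect effect = a·b = 3b

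For ρ = 0.2: b = 0.30 / (1.25 + 1.684) = 0.102, so the indirect effect is 0.31 SD.

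A simulation on the same assumptions (330 per arm from Update on study progress, 1,000 replicates, clustering ignored) agrees:

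| ρ | b | a·b by formula | a·b simulated, total effect 0 | runs with significant indirect effect | median share mediated if total effect is 0.40 SD |
|---|---|---|---|---|---|
| 0 | 0 | 0.00 | 0.00 | 5.5% | 0% |
| 0.1 | 0.054 | 0.16 | 0.16 | 65% | 41% |
| 0.2 | 0.102 | 0.31 | 0.31 | 99.7% | 76% |
| 0.4 | 0.170 | 0.51 | 0.51 | 100% | 127% |

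Two comparisons isolate the cause. With nominations only, the arm difference and the indirect effect are both zero, and at most 0.3% of runs are significant. With proximity ties recorded in both arms (ρ = 0.2), both are again zero, with about 5% of runs significant.

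**4. How far the size depends on the assumptions**

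A second set of runs used fewer ties (nominations Poisson with mean 3, capped at 5) and SD = 1,600 / 0.40 = 4,000 steps. One added tie on average gave a spurious indirect effect of 159 steps (159/1,600 = 10%) at log-slope 0.2 and 284 steps (18%) at 0.4. Two added ties gave 481 (30%) and 900 (56%). At the same slope of 0.2, the answer is therefore 10%, 30% or 76% according to whether one, two or three ties are assumed.

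**The case against.** Several points on the other side have force.

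- **No merging rule is stated.** The sentence says supplemented, in a condensed article. A reader might infer that the 6-month mediator is the simple sum of both sources, and so must rise at 6 months and fall at 18. The document does not say that; it assigns nominations, not proximity data, to those time points. The core point survives, because a separate proximity variable would still be empty for controls.
- **The second path is not built in.** A reader might infer that ties are partly the step count itself, so that false mediation is guaranteed. The outcome comes from a sealed pedometer worn for 7 days. Ties come from another instrument, near the workplace, and presumably need a second participant close by. A positive association is likely but not automatic, and without it the indirect effect is about zero (ρ = 0 above). This stands.
- **The illustration counts ties, whereas the plan names density and centrality.** Density need not rise when contacts are added, so even the direction may differ by measure. This stands, and it is a further reason not to quote a size.
- **There is a legitimate use.** Objective 6(a) concerns uptake and use of the loyalty card, which exists only in the intervention arm. Proximity variables create no between-arm artefact there.
- **Controls' lack of keyfobs is inferred.** That is so, but nothing in the document points the other way.
- **The plan already urges caution.** Its caution covers functional form and omitted variables, not a mediator measured differently by arm.

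**Conclusion.** The concern holds in a limited form. As written, the plan allows a variable that can exist only in the intervention arm, and only in months 0–6, to enter models that split the intervention-versus-control effect. The arm difference in any such variable is then at least partly a product of measurement. This rests on one inference, that controls carry no keyfobs before month 18.

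A false indirect effect needs one further condition: that ties track steps. This is likely because of how ties are logged, but the document does not establish it. The size cannot be determined. The illustrative figures run from nothing to more than the total effect and should not be quoted as estimates for this trial; they also ignore clustering and use tie counts.

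It would go too far to conclude that Objective 6 will be answered wrongly. What is affected is one family of mediators in a secondary analysis. The primary 6-month comparison and its repeat at 18 months do not use these variables.

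**What to change.** In Mediation analyses, replace the statement that nomination networks are supplemented by proximity data with two separate statements:

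1. In the models for initiation and maintenance that divide the intervention-versus-control effect into direct and indirect parts, network variables are derived from colleague nominations only.
2. Variables derived from keyfob proximity are used only within the intervention arm: to describe co-walking, to characterise dose, and to study uptake and use of the loyalty card under Objective 6(a).

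This is a wording change and needs no new data. The cost is that the between-arm models lose the proximity detail. Nominations are not scheduled at 4 weeks, so the initiation model would have only baseline nominations. These precede randomisation and can act as covariates or moderators but not as mediators. The text should say so.
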